#### Measures

##### Screening

The screening survey will include a demographic questionnaire to assess inclusion criteria in addition to the self-report measures outlined in the following subsections.

###### Mental Health History Survey

The mental health history survey includes items to identify individuals whose linguistic abilities or cognitive, neurological, or psychiatric condition might interfere with completing study procedures or fully engaging in the intervention.

###### C-SSRS, Screen Version

The screening includes the self-report screen version of the C-SSRS [67], a well-validated and widely used instrument designed to assess suicidal thoughts and behaviors. Endorsement of the C-SSRS ideation item (Have you actually had any thoughts of killing yourself?) will trigger 3 follow-up items, to cover past-month presence of an identified method, intent, and a specific plan. Responding affirmatively to any of these 3 items will result in automatic study exclusion. Regardless of their responses, all participants will be asked an item to evaluate lifetime history of suicidal behavior; those who endorse this item in addition to past-month active suicidal ideation will also be automatically excluded from study participation.

###### PDSQ Prompts

The screening survey includes the Psychosis, Alcohol Use Disorder, and Substance Use Disorder scales of the PDSQ (6 *yes* or *no* items per scale) [66]. Questions regarding psychosis refer to the previous 2 weeks, and substance-related questions cover the previous 6 months. Prospective participants who respond affirmatively to at least 1 of these prompts (on any of the 3 PDSQ scales) will be automatically excluded, based on established clinical cutoffs for this measure [62].

###### Ruminative Responses Scale–Brooding

The Ruminative Responses Scale–Brooding (RRS-B) [13] will be used to assess study inclusion criteria. The RRS-B comprises 5 items to evaluate the dispositional propensity to engage in past-oriented patterns of repetitive negative thinking. Respondents rate prompts on a scale ranging from 1 (*almost never*) to 4 (*almost always*) based on characteristic reactions to dysphoric mood described by each item.

###### Three-Factor Impulsivity Index

Eligibility will be further determined using the Feelings Trigger Action (FTA) scale of the Three-Factor Impulsivity Index (TFII) [9], a 54-item multidimensional measure of trait-like impulsiveness that asks respondents to rate their agreement with each prompt on a scale of 1 (*I disagree a LOT*) to 5 (*I agree a LOT*). FTA includes 26 items describing tendencies to engage in impulsive speech and action in response to emotional states. The TFII includes 2 additional scales derived from factor analysis: Pervasive Influence of Feelings, which comprises 9 items reflecting powerful cognitive and motivational responses to emotion; and Lack of Follow Through, which captures distractibility and lack of perseverance. Pervasive Influence of Feelings is included as a secondary measure of emotion dysregulation (assessed in conjunction with FTA, at baseline).

##### Emotion Dysregulation

Our primary measures of emotion dysregulation will comprise self-reported rumination (RRS-B) and ERI (FTA). The secondary indices of emotion dysregulation further include EMA indices of daily negative affect, rumination, and ERI, in addition to scores on questionnaires capturing conceptually related constructs (Multimedia Appendix 1).

##### Psychiatric Symptom Severity

Participants will complete the following questionnaires at baseline, postwaitlist, and postintervention time points to evaluate the hypothesized clinical effects of N-ACT (refer to Multimedia Appendix 1 for the secondary symptom outcome measures).

##### Externalizing Spectrum Inventory–Revised

The Externalizing Spectrum Inventory–Revised (ESI-R) [80] is a 100-item questionnaire that covers 23 facets of externalizing psychopathology, including aggression, alcohol and other substance use problems, and fraudulent behavior. Respondents rate each ESI-R item as *true*, *mostly true*, *mostly false*, or *false*. Items referring to impulsivity (ie, redundant with the TFII) will not be included in the scale totals.

##### Inventory of Depression and Anxiety Symptoms, Expanded Version

The 99-item Inventory of Depression and Anxiety Symptoms, Expanded Version [81], is a validated questionnaire that assesses various emotional syndromes across the internalizing spectrum of psychopathology (eg, anxiety, depression, obsessions and compulsions). This instrument produces scores on 3 major factors (distress, fear, and mania), which are each composed of multiple subfactors (18 in total).

#### Statistical Analysis Plan

Our final target sample size (*n*=80) was derived from power analysis (1-β>0.85), based on hypothesized medium between-groups effect sizes (Cohen *d=*0.35) for the main outcomes of interest (α=.05). Before conducting the analyses, data will be checked for errors, statistical assumptions, and potential confounding variables to examine as covariates. Missing data imputation will also be performed as appropriate; we will present the results with and without imputed values for comparison. Our primary analyses will follow the International Conference on Harmonization E9 statistical principles for clinical trials. In accordance with these principles, we will use intention-to-treat analyses to estimate the main effects of N-ACT, using the final assessment scores of all randomized participants. To augment these findings, we will conduct sensitivity analyses restricted to data from participants who complete preintervention and postintervention assessments and at least 6 of the 8 weekly N-ACT sessions.

Descriptive statistics will be calculated to address the preliminary hypotheses regarding N-ACT’s acceptability and adherence. Mean scores on the Interest or Enjoyment and Value or Usefulness subscales of the adapted Intrinsic Motivation Inventory [82] will serve as our main indices of the N-ACT program’s acceptability (H1); specifically, we predict that participants who complete the intervention will provide average ratings of at least 5 (out of 7) across both scales. We further hypothesize that N-ACT participant adherence and retention will be comparable to those observed in other cognitive remediation interventions (H2); specifically, we anticipate median person-level adherence levels between 70% and 75%, which we expect to decrease at the group level by approximately 5% each week [63,64], with most participants (ie, >66%) completing all 8 N-ACT training sessions [33,52]. Consistent with other cognitive remediation protocol procedures [63], we will calculate percentage adherence for each participant as a function of the number of *completed* N-ACT training task trials divided by the *total* number of trials, that is, individual differences in the “dosage” of training.

We will consider potential confounds before testing key hypothesized effects. Of particular import, we will examine whether participants differ significantly in treatment gains based on assignment to a specific training coach and control for this unintended influence as necessary. Specifically, we will use multivariate analysis of covariance (MANCOVA) to explore the effect of coach assignment (independent variable) on postintervention emotion dysregulation (ie, scores on the TFII-FTA and RRS-B; dependent variables), controlling for scores at initial screening.

The core aim of this pilot trial is to determine whether N-ACT significantly reduces ERI and rumination, as measured by the TFII-FTA and RRS-B, respectively (H3). To achieve this aim and the related objective to explore potential mechanisms, we will conduct parallel 2 (group: immediate N-ACT vs waitlist control condition; between-subjects factor)×2 (time: T1 vs T2; within-subjects factor) mixed MANCOVAs to evaluate whether N-ACT completion is associated with greater pre-postintervention improvement in these 2 primary outcomes compared to the waitlist control condition. Among all participants, T1 will represent data collected at the baseline assessment; for participants assigned to the immediate N-ACT group, T2 refers to the postintervention assessment, whereas for those assigned to the control condition, T2 refers to the postwaitlist assessment. Thus, these models will not include postintervention data for participants initially allocated to the waitlist, permitting direct comparisons of the slope of change over time associated with completing N-ACT or the waitlist period. The key index of treatment effect in all MANCOVA models will be the group×time interaction. We will also perform a parallel set of multivariate cluster-robust general linear models with time (T1: baseline time point vs T2: postintervention time point) as the sole regressor on key outcomes of interest, which will include all participants who complete N-ACT (regardless of initial group or condition assignment) to maximize statistical power.

In addition to testing the hypothesized effects on emotion dysregulation, mixed MANCOVA and multivariate cluster-robust general linear models will be used to evaluate performance changes over time on (1) 2 hot executive functioning tasks (ESST and MAFT), which will be used to assess the hypothesized effects on the targeted aspects of affective control (H4); and (2) one hot (MAFT) and 2 cold (Digit Span Backward and SST) executive functioning tasks, which will be used to ascertain transfer to the nontargeted cognitive processes (H5). We will specifically derive key dependent variables from the ESST (valence-specific indices of stop-signal reaction time) and the MAFT (valence-specific indices of accuracy) to assess intervention-related changes in emotional response inhibition and emotional working memory, respectively. We will similarly calculate summary metrics of hot affective flexibility from the MAFT (valence-specific indices of accuracy and reaction time on less frequent “switch” trials prompting emotional reactions instead of working memory recall [73]) as well as cold working memory, updating from the Digit Span Backward (mean span) and cold response inhibition from the traditional SST (stop-signal reaction time) to evaluate near and far transfer of hypothesized N-ACT training effects, respectively.

Finally, we will perform a complementary set of secondary analyses (ie, mixed MANCOVA and multivariate cluster-robust generalized linear models) to explore the hypothesized downstream effects of N-ACT on changes in psychiatric symptom severity (H6). We will use dimension-reduction techniques (eg, confirmatory factor analysis) to extract the summary indices of internalizing and externalizing symptoms from the Inventory of Depression and Anxiety Symptoms, Expanded Version and ESI-R, respectively. Statistical models will use these latent factors as dependent variables, potentially providing preliminary evidence for the efficacy of affective control training as a transdiagnostic intervention to address psychopathology (via diminished emotion dysregulation; refer to Multimedia Appendix 1 for more information). Support for this hypothesis will motivate future work to more directly and precisely examine the effectiveness of the N-ACT program in sufficiently powered samples of patients with psychiatric conditions.

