**Conclusions:**

This pilot randomized waitlist-controlled trial is designed to assess the initial efficacy, feasibility, and acceptability of N-ACT, a novel cognitive remediation approach developed to address 2 key contributors to psychopathology: ERI and rumination. The N-ACT program uses computerized adaptive behavioral tasks to strengthen the affective control processes theoretically and empirically linked to ERI and rumination. We hope this work will help inform future studies with sufficient statistical power to ascertain whether enhancing affective control through cognitive training (N-ACT) produces downstream reductions in psychiatric symptoms via improved emotion regulation.

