### This Study

#### Overview

This pilot randomized waitlist-controlled trial will enroll adult participants with high rumination or ERI scores. The primary aim of this study is to examine the acceptability, feasibility, and efficacy of N-ACT as a novel therapeutic approach to reduce rumination and ERI by improving 2 facets of affective control: emotional working memory and emotional response inhibition. Secondarily, we will test the effects of N-ACT on behavioral indices of ability transfer as well as on other subjective measures of emotion dysregulation (beyond trait rumination and ERI) and psychopathology symptom severity (refer to Multimedia Appendix 1 for details). Finally, we will conduct exploratory analyses to examine the potential mechanisms that might influence predicted changes in emotion dysregulation, informing future work to systematically test these effects in a sufficiently powered sample. In addition to performing intent-to-treat analyses, we will conduct sensitivity analyses to evaluate the extent to which program adherence predicts the hypothesized effects.

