After the baseline assessment (laboratory session, questionnaires, and EMA), we will randomly assign participants to receive active treatment (ie, N-ACT without delay) or the waitlist control condition, unblinded, using an asymptotic maximal procedure to achieve a maximally tolerated imbalance of 2, while maintaining a 1:1 allocation ratio between the 2 trial arms [63]. Participants in the active N-ACT group will begin the intervention, which consists of 8 weekly coached training sessions, within 1 week after baseline EMA. We will recontact waitlist control participants after a period equivalent to the intervention duration (ie, 2 months) to complete a second (postwaitlist) assessment session and EMA before starting the N-ACT program for the following 8 weeks. After the intervention, participants will be asked to complete a second week of EMA, and then a postintervention assessment session with comparable measures to baseline. We will recontact waitlist control participants approximately 10 weeks after their (prewaitlist) baseline assessment session to complete a second (postwaitlist) assessment and 1 week of EMA, parallel with the pre-intervention assessment procedures of the N-ACT group,. The waitlist group will then be offered 8 weeks of N-ACT, followed by a second week of postintervention EMA, and then a final assessment session. In sum, we will follow participants assigned to receive the intervention without delay for 12 weeks (3 mo) and those assigned to the waitlist control group for 22 weeks (5.5 mo). This delayed intervention randomized waitlist-controlled trial design enables us to offer all interested participants the opportunity to participate in the program and maximizes our ability to rapidly accrue a sufficiently sized sample for analyses. Figure 1 demonstrates the flow of potential participants through the study procedures.

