### Study Procedures

#### Recruitment and Screening

We will invite up to 500 adults to complete preliminary screening procedures and an estimated 100 participants to complete the initial baseline assessment session. After accounting for 20% expected attrition, we expect 40 participants in each condition to complete all study procedures.

Study advertisements will be posted locally in public spaces and distributed by web (eg, via email listserves, Craigslist, and social media sites). We will also administer a prescreening survey to students enrolled in psychology classes at the University of California Berkeley, and we will invite students who meet the preliminary inclusion criteria based on those responses to take part in the study. Potential participants (recruited either from the community or from the student participant pool) will be directed to our website, where they can view additional details about the trial. We intend to recruit only secondarily from the student participant pool to supplement community-based recruitment, which will constitute most of the targeted sample. All questionnaires, including screening items, will be administered through REDCap (Research Electronic Data Capture; Vanderbilt University) software [65], which will also be used for the secure storage of collected data.

After providing informed consent, interested individuals will complete the brief web-based screening via REDCap to assess preliminary eligibility. The inclusion and exclusion criteria are presented in Textbox 1.

Inclusion and exclusion criteria.

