### Limitations

The potential impact of this work should be considered in the context of several limitations. Regarding the study sample, we will make every effort to maximize participant diversity and, accordingly, the generalizability of our findings; however, the modest target sample size (n=80) for this pilot trial will constrain our ability to ensure adequate representation of all psychiatric symptom types and severity levels. Relatedly, patients with acute symptoms of alcohol or substance use disorders and psychosis will be excluded. Additional studies will thus be necessary to elucidate the putative mechanisms identified in this work. Although our protocol incorporates a variety of well-validated multimodal measures to assess key constructs, 1 of the 2 primary behavioral outcomes will be derived from the MAFT, which is a novel task developed for this study. This limitation is somewhat lessened in that the MAFT includes design elements drawn from existing tasks that are widely used to index working memory and shifting and switching (eg, other emotional n-back procedures [73]). Finally, we see 2 core needs for enhancing the N-ACT intervention if the initial findings are promising. The current N-ACT intervention is limited in its scope of training around transfer to real-world tasks. Others have more extensively integrated ecological elements into cognitive remediation programs, including simulated work situations [83] and compensatory transfer sessions to supplement computerized training procedures [84]. Future work might help clients practice their skills in the context of mood inductions as a method to facilitate skills transfer. It will also be important to consider gamification [85,86] and other techniques to enhance the appeal of training programs.

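### The stated power (above 0.85 at n=80 for a between-groups d of 0.35) does not follow from its own inputs; the plain two-group figure is about 0.34, and the planned test reaches 0.85 only under favourable assumptions that are not stated

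*Protocol article*

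**What the plan says.** The Statistical Analysis Plan section of the protocol article says that the final target of 80 "was derived from power analysis (1-β>0.85), based on hypothesized medium between-groups effect sizes". In the same sentence it gives the effect and the error rate: "Cohen *d=*0.35) for the main outcomes of interest (α=.05". It does not state the test, the sidedness or a pre-post correlation.

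The other inputs are elsewhere in the article:

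- Recruitment and Screening plans for about 100 people at baseline. "After accounting for 20% expected attrition", it says, "we expect 40 participants in each condition to complete all study procedures".
- The Methods Overview randomises after the baseline assessment, "while maintaining a 1:1 allocation ratio between the 2 trial arms".
- The Statistical Analysis Plan makes the group×time interaction in a 2×2 mixed MANCOVA the key index of treatment effect for the two primary outcomes, RRS-B and TFII-FTA (H3). The intention-to-treat analysis covers everyone randomised.
- Limitations refers to "the modest target sample size (n=80) for this pilot trial".

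**The concern.** Sample size, effect, alpha and power appear together in one sentence, so a reader can check them, and the check fails. Taken as written, a between-groups d of 0.35 with 40 per arm is far from 85% power.

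The stated core aim is to determine whether N-ACT significantly lowers both primary outcomes. The power sentence is the only figure that tells a reader how much weight a non-significant group×time result can bear. If true power at d = 0.35 is well below 0.85, such a result says much less than the sentence implies. Anyone who sizes the next trial from this one would also start from a wrong account of what 80 people can detect.

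The word medium adds a small confusion, because the usual benchmark for a medium d is 0.5. The point does not depend on that.

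**Working it through.** **Inputs.** n = 40 per arm (Recruitment and Screening, 1:1 allocation); d = 0.35, alpha .05, claimed power above 0.85 (Statistical Analysis Plan). Two-sided testing is assumed and one-sided is also shown. The pre-post correlation ρ is not given, so a range is used. The attrition arithmetic is consistent: 80/(1 − 0.20) = 100.

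**1. The stated figure from the stated inputs.** Two-sample t test, noncentrality d·√(n/2), df = 2n − 2.

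- 40 per arm: 0.35 × √20 = 1.565, df 78, power **0.34** (one-sided 0.46).
- 50 per arm (all 100 randomised and analysed): 0.41.
- 80 per arm: 0.59.
- Power of 0.85 at d = 0.35 needs 148 per arm by the exact t calculation (147 by normal approximation).
- With 40 per arm, 85% power is reached at d ≈ 0.68.

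The figure above 0.85 is not reproduced.

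**2. Allowing for baseline, one outcome, 40 per arm.** The effective d is 0.35/√(2(1 − ρ)) for a change score and 0.35/√(1 − ρ²) with baseline adjustment.

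| assumed ρ | change score: effective d, power | baseline-adjusted: effective d, power |
|---|---|---|
| 0.5 | 0.350, 0.34 | 0.404, 0.43 |
| 0.6 | 0.391, 0.41 | 0.437, 0.49 |
| 0.7 | 0.452, 0.51 | 0.490, 0.58 |
| 0.8 | 0.553, 0.69 | 0.583, 0.73 |

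Below 0.5 the change score does worse (0.26 at ρ = 0.3). Power of 0.85 needs ρ of about 0.87 (change score) or 0.86 (baseline-adjusted). With 50 per arm the change score gives 0.78 at ρ = 0.8 and 0.89 at ρ = 0.85.

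**3. Two outcomes tested jointly.** Hotelling test on change scores, both outcomes at d = 0.35, between-outcome correlation r: λ = (n/2) × effective d² × 2/(1 + r), on 2 and 2n − 3 df.

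- 40 per arm, ρ = 0.5: 0.48 (r = 0) down to 0.30 (r = 0.7).
- 40 per arm, ρ = 0.7: 0.71 (r = 0) down to 0.47 (r = 0.7).
- 40 per arm, ρ = 0.8, r = 0: λ = 20 × 0.306 × 2 = 12.25, power 0.88.
- 50 per arm, ρ = 0.8, r = 0.3: λ = 11.78, power 0.87.

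The joint test can therefore fall below or rise above the single-outcome figure. It passes 0.85 only when ρ is high and the outcomes are weakly correlated, or when more people are analysed as well.

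**4. Where a figure just above 0.85 does arise.** Three calculations give 0.871, each with noncentrality λ = 9.8:

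- a paired test in 80 people with a within-person effect of 0.35: 80 × 0.35² = 9.8;
- a between-groups F test with f = 0.35, which is d = 0.70: 80 × 0.35² = 9.8;
- an interaction test with f = 0.175, two measurements and ρ = 0.5: 80 × 0.175² × 2/0.5 = 9.8, which is a 0.70 SD difference in change.

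With f = 0.0875, the value for a 0.35 SD difference in change at ρ = 0.5, the interaction test returns 0.34.

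**5. Expected precision, 40 per arm.** The 95% CI half-width is t(0.975, 78) × √(2/40) = 1.991 × 0.2236 = 0.445 SD unadjusted. Multiplying by √(1 − ρ²) gives 0.39 SD at ρ = 0.5 and 0.32 SD at ρ = 0.7.

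**The case against.** The strongest reply is that 0.34 is not the power of the planned analysis. It belongs to a post-only comparison, or to a change score at ρ = 0.5. The planned test uses baseline and two outcomes, and intention-to-treat may bring in about 100 people. Some combinations then pass 0.85. This stands: a reader might infer that the design's power is 0.34, or that 0.85 is out of reach, and the article supports neither reading. It does not rescue the sentence, because the assumptions needed are favourable and none is stated.

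A reader might also infer that a null result will be taken as evidence against N-ACT. The article sets no such rule. It calls the trial a pilot, lists the modest sample as a limitation, and in the Discussion leaves a fully powered trial to later work. Those caveats soften the risk without correcting the figure.

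Nor should two phrases about future power be read as a flat contradiction of the power claim. In the Abstract, the hope to "inform future studies with sufficient statistical power to ascertain whether enhancing affective control" yields downstream symptom reductions concerns psychiatric symptoms. In the overview of This Study, "informing future work to systematically test these effects in a sufficiently powered sample" refers to exploratory mechanism analyses. Neither is about H3.

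Finally, the matches at 0.871 do not prove where the error came from. The calculation is not shown, so a within-person effect or a doubled d is only a plausible source.

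**Conclusion.** The power sentence is wrong as written: n = 80, a between-groups d of 0.35 and alpha .05 do not give power above 0.85. The plain two-group figure at 40 per arm is about 0.34, and the effect detectable with 85% power is about 0.68, nearly twice the stated effect.

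For the planned group×time test the claim is unsupported rather than impossible. The single-outcome ranges, 0.34 to 0.69 (change score) and 0.43 to 0.73 (baseline-adjusted), rest on assumed correlations of 0.5 to 0.8, two-sided testing and 40 per arm. The joint-test figures further assume the same d of 0.35 on both outcomes. The 50-per-arm figures assume that all 100 are randomised and that imputed scores carry as much information as observed ones.

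**What to change.** Rewrite the power sentence so that it names the test, the sidedness, the effect-size metric (between-arm difference at T2, difference in change, or within-person change) and the assumed pre-post correlation. For a multivariate test, add the assumed correlation between the two outcomes. Then do one of the following:

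- keep d = 0.35 and correct the power to about 0.34 unadjusted, with the range by assumed correlation; or
- keep 85% power and restate the detectable effect as d of about 0.68 unadjusted at 40 per arm.

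Drop the word medium. For H3, report the between-arm difference in change with its 95% CI. The expected half-width is about 0.45 SD unadjusted, or about 0.39 to 0.32 SD with baseline adjustment at correlations of 0.5 to 0.7. Add one sentence saying that a non-significant result at this size is not evidence of no effect.

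The cost is a less favourable stated power. No participants, visits or procedures are added, and the article reports recruitment as still to begin.

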#### Data Quality Assurance

The screening survey and assessment questionnaires will randomly incorporate simple “attention checks” (eg, “2 + 2 = ?” and “for our data quality checking, please answer ‘1’ to this question”) to identify patterns of careless responding, which we will supplement by manual review to confirm the validity of self-report data. As previously noted, we will exclude participants who demonstrate patterns of careless responding during the screening questionnaire. Before conducting statistical analyses, research staff will perform comprehensive data cleaning and processing procedures as needed (eg, ascertaining violations of distributional assumptions for parametric tests and comparison with published norms).

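### Covariates for the H3–H6 models are to be found by searching the collected data, and coach adjustment is triggered by a test on the primary outcomes; a prognostic set fixed in advance would serve better

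*Protocol article*

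**What the plan says.** All of this is in the protocol article.

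- **Covariates.** The Statistical Analysis Plan section says that, before the analyses, "data will be checked for errors, statistical assumptions, and potential confounding variables to examine as covariates". It returns to this later: "We will consider potential confounds before testing key hypothesized effects". The H3 models are then described as 2×2 (group by time) mixed MANCOVAs, with the group×time interaction as the index of effect. No covariate is named for them. H4–H6 use the same model type.
- **Coach.** The same section proposes a MANCOVA of postintervention FTA and RRS-B scores on coach, controlling for screening scores. Coach is then to be controlled for as necessary, with no threshold.
- **Design.** The Methods overview randomises participants while "maintaining a 1:1 allocation ratio between the 2 trial arms". T2 is the postintervention assessment in the immediate arm and the postwaitlist assessment in the control arm. Waitlist participants start N-ACT only after that assessment.
- **Sample size.** There are to be 80 completers, 40 per arm, with d=0.35, α=.05 and power above 0.85.

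**The concern.** A confounder search belongs to observational comparisons. Under randomisation a baseline variable is associated with arm only by chance, so what matters about a covariate is whether it predicts the outcome, and that can be judged in advance. Choosing covariates after inspecting the trial's own data makes the fitted model depend on the sample, while the p-value is computed as if the model had been fixed.

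The coach step goes further. Its trigger is a test on the two primary outcome measures, and its result can change the model used for the primary comparison.

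Two things are at stake: whether the H3–H6 tests keep their stated 5% level, and whether a trial of 40 per arm gives up precision that it could have at no cost.

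**Working it through.** **Step 1. The plan's own power figure.** A 2×2 within-between interaction with f = d/2 = 0.175, N = 80 and an assumed T1–T2 correlation ρ = 0.5 has noncentrality λ = f²·N·2/(1−ρ) = 0.030625 × 160/0.5 = 9.8. With 1 and 78 degrees of freedom this gives power 0.871, which meets the stated figure. Neither f = d/2 nor ρ = 0.5 is stated in the article. λ = 9.8 corresponds to a difference in change of √9.8/√20 = 0.70 SD. Whether that is the effect intended is a separate matter; both 0.35 and 0.70 SD are used below.

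**Step 2. Error rate by selection rule.** Simulation with 40 per arm, a change score of SD 1, and 5 or 10 independent candidate covariates, each correlated r with the outcome. The number of candidates and r are assumptions, because the article gives none. There were 6,000 null runs per setting (standard error about 0.3 points).

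| Rule | 5 candidates, r=0.1 | 5, r=0.3 | 10, r=0.3 |
|---|---|---|---|
| Fixed set | 5.6% | 5.2% | 5.2% |
| Imbalanced at p<0.05 | 5.5% | 4.0% | 2.8% |
| Imbalanced at p<0.10 | 5.4% | 3.3% | 1.6% |
| Correlated with pooled outcome at p<0.05 | 5.4% | 5.1% | 5.3% |

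A separate set of runs under imbalance selection gave 3.7% to 5.1%. So an imbalance rule is conservative if the candidates are prognostic and harmless if they are not. Selection on the pooled outcome is close to nominal.

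**Step 3. Precision forgone, many covariates.** Power at 0.70 SD with five candidates (3,000 runs):

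- r=0.3 (jointly 5 × 0.09 = 45% of outcome variance): fixed set 98.3%, imbalance-selected 89.4% to 90.2%, unadjusted 87.7%.
- r=0.1 (jointly 5 × 0.01 = 5%): fixed set 87.8%, imbalance-selected 88.0% to 88.5%, unadjusted 88.6%.

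The gain depends wholly on prognostic strength. Nothing in the article supports 45% for any available set.

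**Step 4. Precision forgone, T1 alone.** For two measurements of SD 1, the group×time test is a comparison of change scores, with SD √(2(1−ρ)). ANCOVA has residual SD √(1−ρ²). Two-sided power is approximately Φ(d√(n/2)/SD − 1.96), and with d=0.35 and n=40, d√(n/2) = 0.35 × √20 = 1.565.

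| ρ (assumed) | SD, change | Power | SD, ANCOVA | Power |
|---|---|---|---|---|
| 0.5 | 1.000 | 0.347 | 0.866 | 0.439 |
| 0.7 | 0.775 | 0.524 | 0.714 | 0.592 |

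The gain is 7 to 9 percentage points. A simulation of T1 plus two weak covariates gave about 0.42 to 0.58, against 0.31 to 0.51 for the group×time test. Almost all of the gain therefore comes from T1.

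**Step 5. Coach.** At T2 only the immediate arm has been coached. Coach is nested in arm: indicators for the coaches, set to zero on the waitlist, add up to the group indicator. Coach therefore cannot confound group×time in the ordinary sense. Entering it in that model either makes the group term inestimable or turns it into one reference coach against the waitlist.

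**The case against.** The best reply is that a journal article may leave the covariate list to a fuller plan, and this one says that hypotheses and analyses were preregistered, in a record not shown here. That covers the absence of a list or threshold. It does not cover the text as written, which states a search and an outcome-triggered adjustment; a fixed list would have to replace that text.

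It is also fair that the power gain is small unless the covariates are prognostic. Recruitment source and eligibility route may add little beyond T1.

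Three stronger readings are tempting, and the document does not support them.

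- **Covariates chosen to favour the result.** That would inflate false positives, but both sentences place the check ahead of the analyses or of the hypothesis tests, and neither describes picking by treatment effect.
- **Staff handling the data see the arms.** A reader might infer this from "active treatment (ie, N-ACT without delay) or the waitlist control condition, unblinded". Those words describe allocation; the article does not say who sees arm labels during cleaning.
- **Inconvenient T2 records may be dropped.** Questionnaires carry attention checks, "which we will supplement by manual review to confirm the validity of self-report data", but exclusion for careless responding is stated only at screening. The primary analysis is to use the final scores of all randomised participants.

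**Conclusion.** The point holds as a choice of method that should be improved. The plan picks covariates for a randomised comparison by searching the collected data, and it lets a test on the primary outcomes decide on an adjustment that does not fit the primary contrast.

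Without a stated rule, the most that can be said about error is that the tests may not keep exactly 5%. Selection by imbalance errs on the conservative side, with simulated sizes from 1.6% up to nominal, depending on the number and strength of the candidates. No inflation of false positives is shown.

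The firmer loss is precision: about 7 to 9 points of power at d=0.35 from not using T1 as a covariate, if the T1–T2 correlation is 0.5 to 0.7. The additional gain from other baseline variables is probably small.

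**What to change.** - Replace the confounder search with one adjustment set for all H3–H6 models, named now and taken from data collected before randomisation: the T1 value of the outcome, recruitment source (student pool or community) and eligibility route (rumination, impulsivity or both).
- Make T2 the dependent variable and group the effect of interest (ANCOVA form, multivariate where there are several outcomes). T1 cannot be both a level of the time factor and a covariate.
- Report the model without these covariates as a sensitivity analysis.
- Remove the outcome-triggered coach adjustment from the primary group comparison, and report coach effects separately among those who received N-ACT.
- As a minor addition, and not because the plan is in error here, review the validity of T1 and T2 questionnaires on a file without arm labels.

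The cost is wording, plus withholding one column during the review. Recruitment, visits and participants are unaffected. The one downside is that a prognostic variable noticed late can be used only in a sensitivity analysis.
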